## Methods/design

### Study design

The WARRIOR-trial (Wrist and Ankle fractures Routine RadIOgraphy Reduction) is a multicenter randomized controlled trial using a non-inferiority design.

The trial includes two study populations: distal radius fracture patients and ankle fracture patients. The interventional effects will be analyzed separately for each type of fracture as independent studies. The same design and research questions apply for both studies.

The study will be conducted in three academic hospitals in The Netherlands (Leiden University Medical Center (LUMC), VU University Medical Center Amsterdam (VUmc) and University Medical Center Groningen(UMCG)). This study is approved by the Medical Ethics Committee LUMC for all participating centers (Number P14.086). The trial is registered in the Dutch Trial Register (Nederlands Trial Register NTR4610, registration date 22 June 2014). Study results will be reported following the Consolidation of Standards of Reporting Trials guidelines [12,13].

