### Randomization

Randomization of patients will be carried out after obtaining written informed consent using an online randomization program (ProMISe, www.clinicalresearch.nl). Randomization will be stratified by center, type of fracture (distal radius or ankle) and treatment (conservative or surgical). Patients will be randomized into the following two groups.

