#### Group 2 – reduced imaging

Group 2 will receive the same clinical evaluations as the usual care group; however, no routine radiographs will be performed beyond the initial 2 weeks. Radiography during follow-up beyond the initial 2 weeks will be allowed if any of the following are present: new trauma to the distal radius or ankle; pain score >6 on the 11-point visual analogue scale (VAS); loss of range of motion (ROM); neurovascular symptoms; at the discretion of the clinician, in which case the indication for radiography is to be recorded in the medical records.

Aftercare apart from radiology will be identical for both study groups and according to the local standards.

At 6 and 12 weeks, 6 months and 1 year, patients will be requested to fill out the questionnaires. The patient can chose between a paper version or a web-based version of the questionnaire. Reminders will be sent when necessary, and attempts will be made to track drop-outs if possible. An overview of follow-up and measurements is provided in Table 1.

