**Table 1 Tab1:** **Flowsheet**

	**ER**	**Week 1**	**Week 2**	**Week 6**	**Week 12**	**Week 26**	**Week 52**
Written patient information	X						
Randomization			X				
Baseline characteristics			X				
Radiographs							
Group 1		X*	X*	X	X	○	○
Group 2		X*	X*	○	○	○	○
Visual analogue score			X	X	X	X	X
Function scores (OMAS/AAOS or DASH/PRWHE)			X	X	X	X	X
Quality of Life (SF-36/EQ5D)			X	X	X	X	X
Self-perceived recovery				X	X	X	X
Direct and indirect healthcare costs				X	X	X	X
ROM				X	X		
Complications		X*	X*	X	X	X	X

*Standard Protocol first 2 weeks. X, Measurement collected at each time point; ○, radiography only when clinically indicated; AAOS, American Academy of Orthopaedic Surgeons; DASH, Disabilities of the Arm, Shoulder and Hand Score; EQ5D, EuroQol-5D; ER, emergency room; OMAS, Olerud and Molander Ankle Score; PRWHE, Patient-Rated Wrist and Hand Evaluation; ROM, range of motion; SF-36, Short form-36.

Subjects can leave the study at any time for any reason if they wish to do so without any consequences; patients randomized to Group 2 will revert to the usual care, the care according to the current protocol, after leaving the study.

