### Sample size calculation

For both types of fractures (distal radius and ankle), the sample size was determined separately for both patient groups. Based upon a margin of non-inferiority, which is often the smallest value with a clinically important effect [29], of 9 points on the DASH and OMAS (which is based upon what is assumed to be clinically significant [30]) and a standard deviation of 14 [31] and 20 [32], respectively, 70 distal radius and 142 ankle fractures are necessary to demonstrate non-inferiority (power 0.85, alpha 0.05).

To enable a sensitivity analysis for evaluating the study outcomes for two relevant subgroups (that is, conservatively and surgically treated patients), more patients are needed. Based on the empirical treatment ratio for conservative:surgical of 8:2 for distal radius fractures and 5:5 for ankle fractures, we calculated that 142/0.5 = 284 patients with ankle fractures and 70/0.2 = 350 patients with distal radius fractures will need to be included. Accounting for a 10% loss to follow-up means 312 patients with an ankle fracture and 385 patients with a distal radius fracture are to be recruited.

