### Statistical analysis

Data will be analyzed using the IBM SPSS version 20 or higher (Armonk, NY: IBM Corp.). Characteristics of the patients in the treatment groups will be presented using descriptive statistics (mean ± standard deviation, median (range) or proportion) to assess if balanced groups were obtained after randomization.

The data analysis will be conducted according to the intention-to-treat principle, with a normal approximation for all questionnaires at 6, 12, 26 and 52 weeks for both types of fractures. For analysis of the primary study outcome, linear and generalized multilevel analyses will be used accounting for dependency within hospitals, clinicians and patients over time (four-level model). This means, among other things, that the data are to be analyzed longitudinally and, thus, the follow-up measurements are to be incorporated in the analyses. Results will be expressed as confidence intervals and these will be subsequently compared to the margin of non-inferiority in order to make inferences about the non-inferiority of the new intervention strategy. In addition to crude analyses, all analyses will also be adjusted for pre-defined prognostic factors, such as age, gender and fracture type. In a secondary analysis, a per-protocol analysis will be conducted which will account for ‘contamination’, meaning those randomized to the intervention group but nonetheless requiring follow-up imaging not allowed in the original treatment design (because there was a clinical indication for imaging).

The secondary clinical outcome measures of quality of life and pain will be analyzed in the same way as the primary outcome measure. The secondary outcome measures of ROM and complications will be compared between the ‘usual care’ group and the ‘reduced images’ group over time.

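### Neither the crude nor the adjusted result is named as decisive for non-inferiority, and the named adjustment set includes neither the week-2 function score nor the conservative/surgical stratum

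*Protocol article*

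**What the plan says.** Under Statistical analysis, the article plans a longitudinal multilevel model of the questionnaires at weeks 6, 12, 26 and 52, "accounting for dependency within hospitals, clinicians and patients over time (four-level model", and compares the resulting confidence intervals with the margin. Crude analyses are planned, and besides them "all analyses will also be adjusted for pre-defined prognostic factors, such as age, gender and fracture type". A later paragraph of the same section, on missing data, adds correction for baseline covariates thought to be related to outcome, for condition-related variables and for variables related to missingness, again by example. No sentence ranks crude against adjusted.

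Under Randomization: "Randomization will be stratified by center, type of fracture (distal radius or ankle) and treatment (conservative or surgical". Under Study design, wrist and ankle patients are analysed separately as independent studies, and "The study will be conducted in three academic hospitals in The Netherlands".

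Table 1 marks the row "Function scores (OMAS/AAOS or DASH/PRWHE" at week 2, the randomization visit, and at every later visit from week 6. The text under Group 2 gives the times differently: "At 6 and 12 weeks, 6 months and 1 year, patients will be requested to fill out the questionnaires".

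**The concern.** Three things come together.

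- **Two unranked results.** The crude and adjusted intervals can fall on different sides of the margin. The plan does not say which one then carries the conclusion.
- **Two useful variables unnamed.** The week-2 score is neither an analysed outcome time nor a named covariate. The treatment stratum was thought important enough to stratify on and to enlarge the sample for, yet it is absent from the crude model and not named for the adjusted one. The named factor that looks closest, fracture type, is defined under Randomization as wrist or ankle. In that sense it does not vary within either analysis.
- **Doubt whether the baseline score is collected.** Table 1 schedules it and the text on questionnaires does not list it. If a site follows the text, the score cannot be recovered later.

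At stake are precision already provided for by the design and a clear rule for the primary conclusion.

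**Working it through.** **Inputs from the article (Sample size calculation).** Margin "of 9 points on the DASH and OMAS"; "a standard deviation of 14 [31] and 20 [32], respectively"; power 0.85; alpha 0.05; base N 70 and 142; enlarged N 350 and 284; conservative:surgical 8:2 (wrist) and 5:5 (ankle). **Assumed:** 1:1 allocation, true difference zero, correlation r between week-2 and follow-up score of 0.3 to 0.5, and a surgical–conservative difference d of 5 to 15 points. The article gives neither r nor d.

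**1. The plan's own figure.** n per arm = 2(z₁₋α + z₀.₈₅)² SD²/9², with one-sided alpha 0.05.
- Wrist: 2(1.645 + 1.036)² × 196/81 = 34.8, so 35 per arm, total 70.
- Ankle: 2(1.645 + 1.036)² × 400/81 = 71.0, so 71 per arm, total 142.

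Both reproduce, so the stated N corresponds to one-sided 5%. No allowance for covariates is built in.

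**2. Week-2 score as covariate, single time point.** SE = SD √[(2/n)(1 − r²)]; power = Φ(9/SE − 1.645).

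| Sample | r = 0 | r = 0.3 | r = 0.5 |
|---|---|---|---|
| Wrist, 35 per arm: SE; power | 3.35; 0.85 | 3.19; 0.88 | 2.90; 0.93 |
| Ankle, 71 per arm: SE; power | 3.36; 0.85 | 3.20; 0.88 | 2.91; 0.93 |
| Wrist, 175 per arm: SE; power | 1.50; >0.999 | 1.43; >0.999 | 1.30; >0.999 |
| Ankle, 142 per arm: SE; power | 2.37; 0.984 | 2.26; 0.990 | 2.06; 0.997 |

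The first two rows are the planned sizes of the surgical wrist subgroup (0.2 × 350 = 70) and of each ankle subgroup (0.5 × 284 = 142). The last two are the full samples. There the distance from estimate to one-sided 95% bound (1.645 × SE) shrinks from 2.46 to 2.35 or 2.13 points (wrist) and from 3.90 to 3.72 or 3.38 points (ankle).

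**3. Treatment stratum left out.** With surgical share p, the stratum explains R² = p(1 − p)d²/SD² of the variance. Randomization balances it between arms, so the model SE is too large by 1/√(1 − R²), and actual alpha = 1 − Φ(1.645/√(1 − R²)).

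| d (assumed) | Wrist: SE factor; alpha | Ankle: SE factor; alpha |
|---|---|---|
| 5 | 1.010; 0.048 | 1.008; 0.049 |
| 10 | 1.043; 0.043 | 1.033; 0.045 |
| 15 | 1.107; 0.034 | 1.079; 0.038 |

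The error moves in the conservative direction only.

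**4. Three hospitals as a random level.** This was simulated with 6000 trials per setting, hospitals holding 50%, 30% and 20% of patients, randomization stratified by hospital and treatment, the true difference at the margin, one time point and no clinician level. With no stratum effect and an assumed intraclass correlation of 0.05, type I error at nominal 0.05 with random versus fixed hospital effects was 0.0508 v 0.0510 (N = 142), 0.0478 v 0.0480 (N = 284) and 0.0507 v 0.0508 (N = 350). Mean SEs differed by about 0.2% at most. The hospital variance was estimated as zero in 14% to 50% of trials across all settings (intraclass correlation 0.01 or 0.05).

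**The case against.** The strongest reply is that nothing is excluded. Both covariate lists are given by example, the factors are described as defined in advance, and the missing-data paragraph's wording on outcome-related baseline covariates and condition-related variables could cover both the week-2 score and the treatment stratum. A condensed article may leave the full list to the analysis plan. This stands as far as it goes: the variables are unnamed, and a reader who inferred that the adjusted model leaves them out would go beyond the text. It does not answer the rest. The crude model omits both variables however the lists are read, the article puts crude and adjusted side by side without ranking them, and one of the three named factors is void in the article's own sense.

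A reader might also infer that three hospitals as a random level, or the missing stratum, threatens the error rate. Neither is supported. Arms are compared within hospital, so the treatment contrast is practically unchanged, and centre, itself a stratification factor, is in the model. The missing stratum makes a false claim of non-inferiority less likely. The simulation does not test whether the full four-level model converges.

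The power gains belong to the subgroup sizes, rest on an assumed r, and use a single-time-point formula where the plan is longitudinal; all three limits stand. Within the conservative and surgical subgroups the treatment stratum is constant, so only the week-2 score helps there.

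Finally, the text on questionnaire times can be read as listing follow-up only, since it refers to Table 1 for the overview. That reading is possible, but the two places should agree.

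**Conclusion.** The point holds as one of specification and precision. The decisive analysis is not identified, and two variables that the design already provides are not secured in it. The size is modest: 9% to 25% less residual variance if r is 0.3 to 0.5. That is worth 3 to 8 points of power at N = 70/142 and mainly a narrower interval at 350/284. Omitting the stratum costs a little further precision (SE overstated by about 1% to 11% for assumed differences of 5 to 15 points). These figures rest on the article's SDs, 1:1 allocation, a true difference of zero and one-sided 5%. The random hospital level is a matter of modelling convenience. The change is worth making because it is nearly free, and the primary conclusion does not depend on it for validity.

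**What to change.** - For each fracture, name one adjusted model as decisive for non-inferiority. Covariates: week-2 DASH or OMAS, treatment stratum as randomized, centre, age, gender and fracture class (the classification used for eligibility, in place of wrist/ankle). Report the crude result as supportive.
- Keep the random effect for patient, and for clinician if it can be estimated. With three centres, fixed hospital effects are an optional simplification that avoids a variance often estimated as zero.
- Reconcile the questionnaire times in the text under Group 2 with Table 1, so that the week-2 score is collected in every patient.

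The cost is wording, ideally settled before outcomes are seen by arm. The stratum and centre are known from randomization, and the week-2 score needs no new data collection if Table 1 is followed.

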#### Group 1 – usual care

Group 1 will receive usual care according to the current national protocol, indicating clinical follow-up as well as radiographic evaluations in the outpatient clinic at 1, 2, 6, and 12 weeks after trauma.

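### The per-protocol analysis defines contamination in the reduced-imaging arm only, so it cannot detect dilution from usual-care patients who miss the late films

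*Protocol article*

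**What the plan says.** The Study design section states that the trial "is a multicenter randomized controlled trial using a non-inferiority design", with wrist and ankle fractures analysed as separate studies. The control procedure is in the Group 1 section, which describes the national protocol as "indicating clinical follow-up as well as radiographic evaluations in the outpatient clinic at 1, 2, 6, and 12 weeks after trauma". Table 1 marks Group 1 films at weeks 6 and 12. The Group 2 section drops routine films after week 2, permits them for listed reasons or at the clinician's discretion, and keeps all other aftercare the same in both arms.

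The Statistical analysis section makes intention-to-treat the main analysis and compares confidence intervals with the margin. It adds a secondary per-protocol analysis to account for contamination, which it defines as "those randomized to the intervention group but nonetheless requiring follow-up imaging not allowed in the original treatment design". It does not say how a Group 1 patient without the week-6 or week-12 film is classified. The only rule on recording imaging is in the Group 2 section and concerns a discretionary film: "in which case the indication for radiography is to be recorded in the medical records".

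**The concern.** The randomized contrast is the late films and nothing else. A Group 1 patient who has no film after week 2 has had, in substance, the imaging of Group 2. If late films matter to outcome, such patients move the usual-care mean toward the reduced-imaging mean. In a superiority trial that would be conservative; in a non-inferiority trial it helps the new strategy pass.

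Intention-to-treat carries this dilution by design. The per-protocol analysis is the place where it could be seen, but its stated rule looks for departures in the other arm. Patients can answer the questionnaires on paper or online, so someone may miss the clinic film and still supply the primary outcome. Missing outcome data will therefore not remove these patients.

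**Working it through.** **Inputs** (Sample size calculation section unless noted)
- Margin: "of 9 points on the DASH and OMAS".
- Spread, for DASH and OMAS in that order: "a standard deviation of 14 [31] and 20 [32], respectively".
- Base totals: 70 for wrist and 142 for ankle, which the plan says "are necessary to demonstrate non-inferiority (power 0.85, alpha 0.05"; sidedness is not stated.
- Enlarged totals before loss to follow-up: 350 wrist, 284 ankle.
- Allocation (Randomization section): "Patients will be randomized into the following two groups"; no ratio is given, so 1:1 is assumed.
- Share m of Group 1 with no late film: not given; assumed 5% to 30%.

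**Step 1: reproduce the plan's sample sizes.** With no true difference, n per arm = 2 × SD² × (z for alpha + z for power)² / margin². With one-sided alpha 0.05 and power 0.85, (1.645 + 1.036)² = 7.19.
- Wrist: 2 × 196 × 7.19 / 81 = 34.8, so 35 per arm and 70 in total.
- Ankle: 2 × 400 × 7.19 / 81 = 71.0 per arm, or 142 in total (strict rounding up gives 72 and 144).

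One-sided 0.025 gives 88 and 178, which do not match. The plan's figures therefore imply one-sided 0.05, used below.

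**Step 2: dilution.** Let the true difference under full adherence equal the margin, 9 points against Group 2, and let a share m of Group 1 have no late film and fare like Group 2. The expected difference is 9 × (1 − m): 8.55, 8.1, 7.2 and 6.3 at m = 5%, 10%, 20% and 30%.

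**Step 3: false non-inferiority rate.** SE = SD × √(2/n per arm), and the rate is Φ((9 − 9(1 − m))/SE − 1.645).
- Wrist, N = 350: SE = 14 × √(2/175) = 1.50.
- Ankle, N = 284: SE = 20 × √(2/142) = 2.37.

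| m | Wrist, N = 350 | Ankle, N = 284 | Base sizes (70 or 142) |
|---|---|---|---|
| 0 | 5% | 5% | 5% |
| 5% | 8.9% | 7.3% | 6.5% |
| 10% | 14.8% | 10.3% | 8.4% |
| 20% | 32.9% | 18.8% | 13.4% |
| 30% | 56.3% | 30.6% | 20% |

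The enlarged samples fare worse because a narrower interval sits around the same diluted estimate. If one-sided 0.025 were used, the enlarged samples would give 8.7% and 22.4% (wrist) and 5.7% and 11.5% (ankle) at m = 10% and 20%, against a nominal 2.5%.

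**Step 4: what the stated per-protocol rule changes.** It acts only on Group 2, so m in Group 1 is the same in both analyses and so is this source of dilution.

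**Limits of the model.** It is a two-group comparison at one time point, not the planned four-level longitudinal model, and it treats m as patients with no late film at all. A patient who misses only one of the two films dilutes less.

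**The case against.** The strongest reply is that the article defines contamination, not the per-protocol set. Excluding non-adherent controls is the ordinary meaning of per-protocol, and a full definition may stand in a document not shown. It is fair that the article nowhere says in so many words that Group 1 patients without films count as adherent; that follows only from a literal reading. But the article did not leave the matter open. It stated what departure the analysis accounts for, and confined it to one arm.

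Several stronger readings are tempting and do not hold:
- **That imaging is documented only in Group 2.** The recording rule covers the reason for a discretionary film, not whether films were taken. Table 1 schedules the Group 1 films as collected measurements, and hospital records should show them.
- **That Group 1 films will often be skipped.** The Background does call late routine films redundant, but it also lists reasons why clinicians take them, and the films are the current national protocol. High adherence is at least as plausible.
- **That any harm beyond the margin would be hidden.** The decision rests on confidence limits, not point estimates. With an assumed true deficit of 12 points and 25% of Group 1 without late films, the expected difference is 12 × 0.75 = 9.0, and false non-inferiority is only the nominal 5%. At 10% it is 12 × 0.90 = 10.8, and the rate is about 0.2% (wrist) or 0.8% (ankle).
- **That scheduled rather than actual films will be costed.** The article does not say so.

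One further objection stands in full. Films may be skipped in patients who are recovering well. Simply excluding them would worsen the usual-care mean and itself favour non-inferiority.

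**Conclusion.** The concern holds as a defect in the stated rule, not as a demonstrated bias. The adherence definition is one-sided, and the departure it omits is one that favours the trial's hypothesis. The direction is clear if late films affect outcome; the size is unknown because no rate of missed films is given. At a true difference equal to the margin, with one-sided alpha 0.05, 10% to 20% of Group 1 without any late film would raise false non-inferiority from 5% to about 15% to 33% for wrist and 10% to 19% for ankle. These are illustrations, resting on the stated SDs, 1:1 allocation, the enlarged samples and full equivalence of such patients to Group 2. Because this concerns a secondary analysis and is cheap to correct, it should be corrected, but it does not undermine the design.

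**What to change.** 1. Take the date of every wrist or ankle film after week 2, in both arms, from the existing records of the three hospitals.
2. Define adherence for both arms. For Group 1: routine week-6 and week-12 films received within stated windows, with no late film distinguished from one missed film. For Group 2, first reconcile the Statistical analysis wording, which calls indicated films not allowed, with the Group 2 section, which allows them.
3. Report Group 1 adherence by centre.
4. Run the per-protocol analysis on this definition, adjusting or weighting for baseline factors and for recovery measured before each film, not by simple exclusion alone. Table 1 schedules function and pain scores at week 2 (before the week-6 film) and week 6 (before the week-12 film). Read the result beside intention-to-treat.
5. Use the same film counts as the imaging volume in the cost analysis.

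The cost is one data extract and a few sentences in the analysis section. The price is a smaller per-protocol set and some selection bias that adjustment will not fully remove, so the analysis supports intention-to-treat and does not replace it.

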**Methods/design:**

In a multicenter randomized controlled trial, 697 patients aged 18 years or older will be included: 385 wrist fracture- and 312 ankle fracture patients. Patients will be randomized into two groups: Group 1 receives usual care, consisting of radiographs 1, 2, 6 and 12 weeks post-trauma; Group 2 receives radiographs beyond the initial follow-up only when clinically indicated. The primary outcome is the overall extremity-specific function. For wrist fractures, this includes the Disabilities of the Arm, Shoulder and Hand Score; for the ankle fractures, this includes the Olerud and Molander ankle score. Secondary outcomes include: healthcare cost, the specific function measured with the Patient Rated Wrist and Hand Evaluation for wrist fractures and American Academy of Orthopaedic Surgeons foot and ankle questionnaire for ankle fractures, pain-intensity, health-related quality of life, self-perceived recovery, and complications. Both groups will be monitored at 1, 2, and 6 weeks and 3, 6, and 12 months.

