The cost questionnaires will be used to perform an economic evaluation, which will be conducted from a societal perspective alongside the randomized controlled trial. The aim of the economic evaluation is to measure, value and analyze total costs of patients with distal radius and ankle fractures and to relate the difference in costs to the difference in effects between the intervention group which will receive only the initial follow-up radiographs (at 1 and 2 weeks) and the comparison (that is, usual care) which will receive imaging at the initial follow-up plus at 6 and 12 weeks. Both cost-effectiveness and cost-utility analysis will be performed. The time horizon of the economic evaluation is 12 months. Sensitivity analyses will be performed to assess the robustness of the results using different assumptions regarding costs and effects.

The underlying assumption surrounding missing data for this study is that the data are missing at random. Therefore, given the mixed model approach for the longitudinal analyses, missing data will not be imputed; however, we will correct for baseline covariates thought to be associated with the outcome, such as age, gender, and variables related to the condition (for example, fracture type), as well as variables thought to be related to missingness. In a sensitivity analysis, complete data sets will be compared to incomplete data sets in order to determine how robust these findings are.

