### Ethical considerations

The study design is in accordance with the Declaration of Helsinki, version Fortaleza (Brazil), October 2013 [33], and in accordance with the Dutch Medical Research Involving Human Subjects Act. Patients will not experience any benefit from participating in the study. No risk is involved for the group receiving usual care (Group 1). In Group 2 without standard radiographs after 2 weeks, the risk is considered minimal because radiographs will be made when clinically indicated.

This study is approved by the medical research ethics committee for all participating centers. The Medical Ethics Committee LUMC acts as central ethics committee for this trial (Number P14.086). An insurance which is in accordance with the legal requirements in the Netherlands (Article 7 WMO and the Measure regarding Compulsory Insurance for Clinical Research in Humans of 23 June 2003) has been obtained. This insurance provides cover for damage to research subjects through injury or death caused by the study. Once a year, information will be provided to the medical research ethics committee on the numbers of subjects included and numbers of subjects that have completed the trial, serious adverse events/serious adverse reactions, and other problems.

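### The per-protocol analysis counts clinically indicated Group 2 radiographs as contamination, although the protocol allows them, so that secondary result would be expected to lean towards non-inferiority

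*Protocol article*

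**What the plan says.** The Study design section states that the trial "is a multicenter randomized controlled trial using a non-inferiority design". Four places make clinically indicated radiographs after week 2 part of the Group 2 strategy:

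- Abstract, Methods/design: "Group 2 receives radiographs beyond the initial follow-up only when clinically indicated".
- Group 2 – reduced imaging: "Radiography during follow-up beyond the initial 2 weeks will be allowed if any of the following are present". The list is new trauma, then "pain score >6 on the 11-point visual analogue scale (VAS); loss of range of motion (ROM); neurovascular symptoms; at the discretion of the clinician". In the last case the indication must be written in the medical records.
- Table 1 marks Group 2 at weeks 6, 12, 26 and 52 with the symbol for "radiography only when clinically indicated".
- Ethical considerations: "the risk is considered minimal because radiographs will be made when clinically indicated".

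The Statistical analysis section makes intention-to-treat the main analysis and adds a secondary per-protocol analysis that is to account for contamination. It defines contamination as "those randomized to the intervention group but nonetheless requiring follow-up imaging not allowed in the original treatment design", with a parenthesis giving a clinical indication as the reason for the imaging. The definition names the intervention group only.

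**The concern.** One event, a Group 2 radiograph after week 2 on a clinical indication, is permitted in four places and described as not allowed in the fifth. The fifth is the one that governs an analysis.

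In a non-inferiority trial, non-adherence can pull the intention-to-treat comparison towards equality, so readers look to the per-protocol analysis as a check. That check is useful only if it sets aside real departures from the assigned strategy. Under the present wording it would single out adherent patients, in one arm, on events after randomization. Pain above the threshold, loss of motion and neurovascular symptoms go with worse function, and the DASH itself measures symptoms and physical function. Group 1 patients with the same signs are left alone. The comparison would set all of Group 1 against a better-recovering part of Group 2, so the check would lean towards the conclusion it is meant to test.

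**Working it through.** **1. The texts side by side.** Take a Group 2 patient who reports pain above the threshold at week 6 and has a radiograph. Under the Group 2 section, Table 1, the abstract and the ethics section, this patient received the assigned strategy. Under the Statistical analysis section, this patient is contaminated. The definition cannot be read as covering only imaging outside the listed indications, because its parenthesis gives the clinical indication itself as the reason. The two statements cannot both stand, and no outside figure is needed to see it.

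**2. The plan's own figures.** Inputs from Sample size calculation: margin 9, SD 14 (DASH) and 20 (OMAS), power 0.85, alpha 0.05. With 1:1 allocation, no true difference and a one-sided 5% test, n per arm = 2·SD²·(1.645 + 1.036)²/9², where the squared sum is 7.189.

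- DASH: 2·196·7.189/81 = 34.8, so 35 per arm, 70 in total (stated: 70).
- OMAS: 2·400·7.189/81 = 71.0 (just above 71), so 71–72 per arm, 142–144 in total (stated: 142).

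One-sided 2.5% gives 88 and 178 and does not reproduce the plan. One-sided 5% is therefore used below. The allocation ratio is not stated, so 1:1 is an assumption.

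**3. Direction.** If a share q of Group 2 is dropped and is on average D points worse than those kept, the Group 2 mean improves by q·D while Group 1 is unchanged. With q = 20% and D = 15 (both assumed), the shift is 3.0 points, a third of the margin. A lower DASH and a higher OMAS are both better, so the shift favours Group 2 on either scale.

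**4. Illustrative size.** Assume the imaged patients are the worst share q on a latent severity score that correlates ρ with the outcome (bivariate normal), and that they are excluded. Then

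shift = ρ · SD · φ(z)/(1 − q), where z is the (1 − q) normal quantile.

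The factor φ(z)/(1 − q) is 0.195 at q = 10%, 0.350 at 20% and 0.497 at 30%.

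| q | ρ | DASH shift (SD 14) | OMAS shift (SD 20) |
|---|---|---|---|
| 10% | 0.3 | 0.8 | 1.2 |
| 20% | 0.4 | 2.0 | 2.8 |
| 20% | 0.6 | 2.9 | 4.2 |
| 30% | 0.6 | 4.2 | 6.0 |

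**5. Effect on the per-protocol conclusion alone.** At a true difference equal to the margin, the chance of a non-inferior per-protocol result is Φ(shift/SE − 1.645), with SE = SD·√(1/n + 1/(n(1 − q))) and n = 175 (wrist, 350/2) or 142 (ankle, 284/2). With no shift it is 5%.

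- q = 10%, ρ = 0.3: SE 1.54 and 2.44; chance 13% (wrist) and 12% (ankle).
- q = 20%, ρ = 0.4–0.6: SE 1.59 and 2.52; chance 34–58% (wrist) and 30–51% (ankle).

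This is a comparison at a single time point. The planned analysis is a longitudinal multilevel model, so these figures only indicate an order of magnitude.

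**The case against.** **Exclusion is inferred.** The text says the analysis will account for contamination; it does not say that the patients are removed. This stands: exclusion is the usual meaning of per-protocol, but it is not stated. The alternatives do not rescue the definition. Moving these patients to Group 1 biases in the same direction, and adjusting for imaging conditions on a marker of poor course that arises after randomization.

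**A reader might infer that the rule strips out the worst Group 2 patients.** The document does not support that. New trauma and clinician discretion are also triggers, and neither ranks patients on function. Selection towards poorer recovery is expected; strict truncation of the worst tail is a modelling device.

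**A reader might infer that the trial's false-positive rate is inflated.** It is not. Intention-to-treat is the main analysis, per-protocol is secondary, and nothing lets the per-protocol result establish non-inferiority alone. The rates in step 5 belong to the per-protocol result only.

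**The size rests on assumptions.** This stands in full. The document gives neither the share imaged nor the correlation, and at the low end the shift is about a point.

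**The article may leave per-protocol rules to a fuller document.** That is fair for a full list of deviations in both arms, so the absence of a Group 1 rule is not claimed as a defect. It does not excuse a definition that is stated and conflicts with the article's own Group 2 section.

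**The economic evaluation.** It describes the intervention as "the intervention group which will receive only the initial follow-up radiographs (at 1 and 2 weeks"). A reader might infer that indicated radiographs would go uncosted. The phrase can be shorthand for scheduled imaging, and the same paragraph sets out to measure total costs, so it is not used as support.

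**Conclusion.** The contamination definition is wrong as written. It contradicts the Group 2 section, the abstract, Table 1 and the ethics section, and it classes adherent patients as deviators in one arm only. If these patients are excluded or moved to Group 1, the per-protocol result would be expected to favour non-inferiority and could falsely corroborate the main result. The direction rests on the pain, motion and neurovascular triggers marking poorer function. The size is not derivable: 0.8–4.2 DASH or 1.2–6.0 OMAS points holds only under exclusion, 10–30% imaged and a correlation of 0.3–0.6. The damage is confined to the secondary analysis, so this is a should-fix.

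**What to change.** Reconcile the Statistical analysis section with the Group 2 section. For the per-protocol set:

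- Group 2 radiographs after week 2 with a recorded indication from the Group 2 list count as adherence, and these patients stay in the set under their assigned arm.
- Only Group 2 radiographs after week 2 without such an indication count as contamination.

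The cost is a change of wording. The protocol already requires the indication for discretionary radiographs to be recorded; the same record is needed for the other listed indications so that the rule can be applied. Sample size and visits do not change. The trial is described as still enrolling, so the wording can be settled before any analysis.
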